| Study Type Hypothesis testing |
| Study Design Longitudinal cohort study |
| Feasibility counts There are approximately 5.5 million patients in England, aged 40+ and with up to standard registration for a period between 1/1/1998 to 31/12/2017 in the CPRD GOLD. Restricting to English practices (linked to HES and ONS) and only including patients fulfilling the eligibility criteria listed below, the expected population is approximately 3.3 million and out of these we expect 216,000 fall events, 230,000 myopathy/muscle pain events and 1,200 intracranial haemorrhage events. |
| Sample size considerations We have based our sample size calculation on the least common of the primary outcomes listed above (intracranial haemorrhage), and used the method developed by Riley *et al.,*^40^ to minimise the potential for overfitting and ensure precise estimates of key parameters. A sample size of approximately 80,000 patients is required for the development of a clinical prediction rule for this outcome, assuming an event rate of 24.6 per 100,000 person years,^41^ a median follow up of 7 years,^42^ a conservative estimate of Nagelkerke’s R^2^ statistic of 0.15 and a maximum number of 40 parameters per model.  Feasibility counts showed that this sample size is adequate for the development of the prediction rules. Since Intracranial bleeding is the rarest of the primary outcomes to be studied, the sample size will be sufficient for all other outcomes of interest. For validation, Vergouwe *et al.,*^43^ consider at least 100 events per sample population to be “substantial” and we will comfortably exceed this in our validation cohorts for each outcome of interest.  For analyses using causal inference methods (propensity score matching and instrumental variable analysis), assuming clinically significant increased rate of each adverse event with treatment of 10%, and an event rate of at least 0.5% per year in the non-exposed group, approximately 88,380 patients (44,190 in each group) and 4,634 events will be required to accurately define the relationship between preventative treatment and adverse events, with 90% power and an alpha of 0.05. |

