| Data/ Statistical Analysis **Prognostic modelling**  ***Aim 1 – prognostic model derivation (primary analysis)***  Where feasible and appropriate, flexible parametric survival models will be derived in the CPRD GOLD for each outcome separately. Baseline survival over time will be estimated using the Royston-Parmar approach of restricted cubic splines on the cumulative log hazard scale. In contrast to Cox regression, this allows a smoothed estimate of the baseline survival function to be derived, and the time period of prediction to be varied, facilitating individualised risk prediction. For the primary analysis, a 10-year period of prediction will be considered. Further sensitivity analyses will be conducted examining a 5-year period. Where insufficient data are available, or modelling procedures become prohibitively complex (computationally), simpler approaches such as Cox regression will be considered.  Each drug class (prescribed in the 12 months prior to the index date) will be entered into the model as a binary variable to allow for multiple treatments to be considered in each model. Where appropriate, models will be constructed with all other variables entered as continuous (not categorised) variables, and potential non-linear trends will be examined. Transformations or fractional polynomials will be used if non-linear trends are detected. Where hazard ratios are not proportional, interactions of effects with time will be included. Further interaction terms, identified in an accompanying systematic review, accounting for treatment effects which differ across specific populations may be included. Where appropriate, models will be reduced and candidate predictors selected for inclusion based on p values of association. Time since cohort entry will be used as the underlying time function in each survival model.  In a further analysis, we will extend the modelling process as described above to account for competing risk of death from other causes. This will produce a model that predicts the risk of adverse events from cardiovascular treatment over time, in the real world where individuals might die from other causes and thus prevent cardiovascular treatment adverse events from occurring. We will again use a flexible parametric modelling framework to estimate the sub-distribution hazard and cause-specific cumulative incidence functions.^45^  Missing data will be handled, under a missing at random assumption, using multiple imputation (see below) followed by Rubin’s rules to combine parameter estimates across studies.  Where feasible and appropriate, each model will be internally validated using the bootstrap method, to allow optimism-adjusted estimates of calibration and discrimination performance to be obtained. Adjustment for overfitting will be undertaken using a uniform shrinkage factor identified from bootstrapping, followed by re-estimation of the cumulative baseline sub-distribution hazard function (and thus baseline cumulative incidence function) to maintain overall calibration between observed and predicted risks. Given the large sample size, overfitting is likely to be small (see sample size calculation above). If bootstrapping is computationally infeasible due to the large sample size, then a smaller random sample of the population will be used or alternative internal validation methods employed such as cross validation.  ***Aim 2 – prognostic model validation***  External model validation will be undertaken using data from CPRD Aurum. The accuracy of risk predictions from each model will be assessed with calibration plots and 5 and 10 years, calibration measures (slope, E/O statistics), measures of overall fit (using pseudo-R^2^ estimates) and discrimination measures (C-statistics and D-statistics).  ***Aim 3 – causal inference analysis***  For most of the outcomes described in this proposal, the association and magnitude of effect with treatment is not well defined in randomised controlled trials. We will therefore undertake causal inference work to examine whether modification of treatment could have an important impact on the risk of adverse events using two causal inference methods: propensity score matching and instrumental variable analysis.  For the propensity score analysis, eligible patients will be matched 1:1 at the index date using propensity scores, which indicate the likelihood a patient will be prescribed treatment on the basis of their known (pre-treatment) characteristics and other known information which might influence the decision to treat. Predictors of preventative drug prescription will be explored in a logistic regression model. Matched patients will be compared using the Cox proportional hazards models, but hazard ratios will only be adjusted by factors unbalanced at baseline which are not already included in the propensity score model. Time since cohort entry will be used as the underlying time function in each model.  For the instrumental variable analysis, GP’s previous antihypertensive prescribing preferences will be used as an instrument to predict the likelihood of actual treatment. Risk of adverse events will be estimated in patients attending a GP considered a high prescriber of preventative medication and compared to those attending a GP considered a low prescriber. If the results from the propensity score matching suffer from unmeasured confounding, they will differ from those of the instrumental analysis. If this is the case, these models will be refined with additional factors to achieve better adjustment and matching. Where all approaches provide similar results, we can be more confident that the findings are accurate and reliable.^46^  A similar approach will be applied to secondary outcomes, for example, memory loss which has been hypothesised as being linked with statins^47^ and is a concern of many patients in practice, but there is no evidence to support this association from trials.^48^ We recognise that the evidence base may change for some outcomes over the next few years, and so the need to test the associations between treatment and certain outcomes may change.  *Subgroup and sensitivity analyses*  Where possible and appropriate, analyses of treatment associations will be examined in subgroups of the population. These will include age, sex, baseline blood pressure and cardiovascular risk, by drug type/dose/intensity and past medical history. Subgroup definitions will be agreed by expert opinion or taken from an accompanying systematic review of previous trials, examining the same topic.  Sensitivity analyses will be undertaken examining risk models for outcomes defined according to both hospital and primary care records. We will also explore the impact of our definition of myopathy and muscle pain, focussing on formal diagnostic codes for myopathy only. Models utilising a 5-year follow-up will be examined as a further sensitivity analysis. The primary analyses will examine the association between treatment and outcomes, assuming treatments are not altered or modified in the future. Where possible, sensitivity analyses will examine treatment entered as time varying covariates, and censor patients who have treatments removed or switched following the index date. |

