| Plan for addressing confounding Two approaches will be taken to determine whether observed associations are potentially subject to residual confounding.^46^ Where all approaches provide similar results, we can be more confident that the findings are accurate and reliable. Further steps will be taken to examine the validity of treatment effect estimates using positive and negative controls: the impact of treatment on an outcome known to be affected by treatment (e.g. cardiovascular disease; positive control) and outcomes not known to be affected by treatment (negative control). Here, we will combine two common but unrelated outcomes to be examined as negative controls: bowel cancer and chronic obstructive pulmonary disease (COPD). If treatment has a significant impact on these negative controls, it suggests that there is something missing in the analysis (i.e. an unmeasurable factor confounding the treatment effect such as being generally unwell or an unhealthy lifestyle) causing an imbalance between the treatment and control groups, rather than a true treatment effect. |

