| Limitations of the study design, data sources, and analytic methods This study focuses on potential harms from adverse events associated with preventative treatments for cardiovascular disease. Such outcomes may be less well recorded in routine electronic health records. For example, initial scoping work suggests the rate of falls documented in the CPRD is between 0.06-0.34% per 1000 person-months. These incidence rates may be less than those reported in smaller previous studies (0.15-6.40% per 1000 person-months) using different definitions, captured via detailed questionnaires and follow-up.^49-52^ Incidence rates are likely to be higher when linked data from HES and ONS are available.^53^ Missing data on certain outcomes may reduce the accuracy of the prognostic models, but should not bias the results provided the data are missing at random and not affected by whether patients are prescribed treatment. To minimise the risk of reporting bias, outcomes in the primary analysis will be defined according to hospital admissions documented in the HES or ONS.  The causal inference work will use an observational cohort design, and as such, there is an inherent selection bias of patients in both exposure and control groups. The impact of this bias will be limited by propensity score methods used to control for confounding, but this approach assumes that all confounding factors are measured and accounted for within the analysis. In the present study, we will examine the validity of this assumption by 1) using an instrumental variable (GP prescriber preference) and examining the association with the outcomes of interest and 2) by studying the impact of treatment on positive and negative controls: hospitalisation and/or death from cardiovascular disease and bowel cancer/COPD. We will conclude the assumption has been met if high GP prescribers have a similar association with outcomes and the treatment itself and treatment is shown to be associated with the positive control, but not the negative control.  *Strategy for dealing with potential errors resulting from multiple testing*  This study will examine multiple outcomes across 3 exposure variables. To avoid potential errors arising from multiple testing, a primary outcome has been clearly defined for each exposure variable. Secondary outcomes are also pre-specified. The primary outcome will be given priority in the final analysis write-up and any related reports and presentations.  Primary and secondary outcomes will be defined using data from Basic inpatient HES and ONS. Sensitivity analyses will explore analyses defining these outcomes using the above sources and read-coded primary care data. The accuracy of such outcome data has been examined previously in patients with acute myocardial infarction and whilst recording of risk factor and co-morbid information was consistent across primary care, hospital admissions and disease registry records, the crude incidence of acute myocardial infarction was underestimated by up to 50% if only one data source was used, compared with using all three sources.^53^ The use of linked CPRD data will ensure outcome data are ascertained accurately. |

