| List of Appendices Appendix 1. Code lists for the primary outcomes |
| Amendments **Amendment 1 – 19/05/2019 (approved)**  **We clarify that aims 1 and 2 (prognostic model derivation and validation) of the study should include the whole population independently of whether patients are new or old users of preventative treatment; the causal inference analyses will focus on new users only:**  *L. Definition of the study population*  Patients will be excluded if they meet the following criteria:  Previous prescription of the exposure variable (antihypertensive, statin or antiplatelet; for causal inference analyses only)  **Amendment 2 – 28/06/2021 (approved 05/07/2021)**  **We have made the following revisions aimed at simplifying the analysis plan in light of the very large sample size and computational time required to conduct each analysis:** *C. Technical Summary / E. Objectives, Specific Aims and Rationale* Aims:  3) Use causal inference methods (multivariable regression, propensity score adjustment/matching, instrumental variable analysis) to examine whether modification of treatment could have an important impact on the risk of adverse events.  *L. Definition of the study population*  Study entry criteria – Patients will enter the cohort on the index date, defined as:   \| **Exposure** \| Antihypertensive therapy \| Statin therapy \| Antiplatelet therapy \| \| --- \| --- \| --- \| --- \| \| **Index date definition** \| 12 months after the first systolic blood pressure reading ≥130 mm Hg \| 12 months after the first coded or calculated CVD risk of ≥5% (equivalent to age ≥50 years for men and ≥60 years for women) \| 3 months after first CVD event \|   *N. Exposures, Outcomes and Covariates*  Positive controls are outcomes know to be affected by treatment (e.g. cardiovascular disease, death)  For causal inference analyses (only), sensitivity analyses will explore outcomes defined more broadly using primary care codes as well. *O. Data/ Statistical Analysis* We no longer plan to conduct an internal validation of the prediction models. The following text from the protocol is therefore redundant:  Where feasible and appropriate, each model will be internally validated using the bootstrap method, to allow optimism-adjusted estimates of calibration and discrimination performance to be obtained. Adjustment for overfitting will be undertaken using a uniform shrinkage factor identified from bootstrapping, followed by re-estimation of the cumulative baseline sub-distribution hazard function (and thus baseline cumulative incidence function) to maintain overall calibration between observed and predicted risks. Given the large sample size, overfitting is likely to be small (see sample size calculation above). If bootstrapping is computationally infeasible due to the large sample size, then a smaller random sample of the population will be used or alternative internal validation methods employed such as cross validation.  *Aim 3 – causal inference analysis*  For most of the outcomes described in this proposal, the association and magnitude of effect with treatment is not well defined in randomised controlled trials. We will therefore undertake causal inference work to examine whether modification of treatment could have an important impact on the risk of adverse events using two causal inference methods: multivariable adjustment, propensity score adjustment/matching and instrumental variable analysis.  For the analysis using multivariable adjustment, Cox proportional hazards models will be used to compare adverse event rates in each experimental group. Estimates will be adjusted for pre-specified variables thought to confound the relationship between treatment and adverse events.  For the analysis using propensity scores, we will conduct separate analyses adjusting for propensity score and matching via propensity score.  *Subgroup and sensitivity analyses*  Where possible and appropriate, analyses of treatment associations will be examined in subgroups of the population. These will include age, sex, baseline blood pressure and cardiovascular risk, by drug type/dose/intensity and past medical history. Subgroup definitions will be agreed by expert opinion or taken from an accompanying systematic review of previous trials, examining the same topic. For computational reasons (whereby only one imputation model is required for all subgroup analyses of each outcome), these analyses will only be undertaken using propensity score adjustment. *P. Plan for addressing confounding* Two approaches will be taken to determine whether observed associations are potentially subject to residual confounding.^46^ Where all approaches provide similar results, we can be more confident that the findings are accurate and reliable. Further steps will be taken to examine the validity of treatment effect estimates using positive and negative controls: the impact of treatment on an outcome known to be affected by treatment (e.g. cardiovascular disease and death; positive controls)  **Amendment 3 – 25.11.2021**  **We have added exploratory analyses using supervised machine learning approaches to address missing data and deal with confounding by indication in the causal inference analyses.** O. Data/ Statistical Analysis ***Aim 3 – causal inference analysis***  For most of the outcomes described in this proposal, the association and magnitude of effect with treatment is not well defined in randomised controlled trials. We will therefore undertake causal inference work to examine whether modification of treatment could have an important impact on the risk of adverse events using two causal inference methods: propensity score matching and instrumental variable analysis.  For the propensity score analysis, eligible patients will be matched 1:1 at the index date using propensity scores, which indicate the likelihood a patient will be prescribed treatment on the basis of their known (pre-treatment) characteristics and other known information which might influence the decision to treat. Predictors of preventative drug prescription will be explored in a logistic regression model. Matched patients will be compared using the Cox proportional hazards models, but hazard ratios will only be adjusted by factors unbalanced at baseline which are not already included in the propensity score model. Time since cohort entry will be used as the underlying time function in each model.  For the instrumental variable analysis, GP’s previous antihypertensive prescribing preferences will be used as an instrument to predict the likelihood of actual treatment. Risk of adverse events will be estimated in patients attending a GP considered a high prescriber of preventative medication and compared to those attending a GP considered a low prescriber. If the results from the propensity score matching suffer from unmeasured confounding, they will differ from those of the instrumental analysis. If this is the case, these models will be refined with additional factors to achieve better adjustment and matching. Where all approaches provide similar results, we can be more confident that the findings are accurate and reliable.^46^  Generative Adversarial Networks (GAN) will also be used to impute missing counterfactual data (unobserved effects of untaken treatments) on an individual level. GAN models are a class of machine learning frameworks that involves the simultaneous training of a pair of deep neural networks in competition with each other. The idea is that the first network, the generator, generates synthetic data samples that are similar to the original samples, while the second network, the discriminator, evaluates the authenticity of the generated samples [1]. Data similarity and fidelity are usually evaluated using well-known metrics such as Maximum Mean Discrepancies [2] and Jensen-Shannon Divergence [3]. While GAN’s initial uses were for imaging applications, its generative capabilities make it naturally suitable for generating missing values that can be used to impute the original samples.  In this work, we build on the intuition that treatment effects estimation and causal inference are a missing data problem, where counterfactuals (unobserved effects of untaken treatments) are missing [4]. Specifically, we plan to use GAN to impute missing counterfactual data, for the samples available in CPRD. By modifying the generator’s goal to accurately impute missing data, and the discriminator’s goal to distinguish between observed and imputed counterfactual values for the same patient record. The model can generate the missing data conditional on the observed values and assigned treatment for each patient as seen in [5, 6]. While useful, the work of [5, 6] are not compatible for time-series data nor for estimating multiple treatment effects, which limits its use in real-life treatment applications. Therefore, we plan to extend such previous works to make them compatible for multiple treatment options and for time-series data to allow for long-term treatment (antihypertensives, statins, antiplatelets) estimation effects for multi-morbid populations as initially proposed in this project.  The proposed GAN approach does not generate new patient samples, but rather generates counterfactual (missing component) conditioned on observed factual data, and outputs a complete record with both factual and counterfactual outcomes to allow for treatment effect estimation for each patient. This approach is naturally immune to re-identification attacks since no new samples are generated, but we will run privacy checks and measures within the data to verify that the model is not copying potential outcomes from patients in the training sample. Example privacy measures that we plan to apply include empirical evaluations such as mathematical privacy definitions such as identifiability [7] that quantifies the probability of re-identification to ensure that no combination of attributes could reveal the identity of a patient. Other privacy evaluation methods include testing that the model is robust against membership inference attacks, where an attacker attempts to determine if a specific patient was used in the training set of the model [8]. Lastly, we will experiment with strict theoretical guarantees such as differential privacy which allow for the model to learn almost nothing about an individual while learning useful information about a population [9].  **References**  [1] Ian Goodfellow, Jean Pouget-Abadie, Mehdi Mirza, Bing Xu, David Warde-Farley, Sherjil Ozair, Aaron Courville, and Yoshua Bengio. Generative adversarial nets. *Advances in neural information processing systems*, 27:2672–2680, 2014.  [2] Arthur Gretton, Karsten M Borgwardt, Malte J Rasch, Bernhard Sch¨olkopf, and Alexander Smola. A kernel two-sample test. *The Journal of Machine Learning Research*, 13(1):723–773, 2012.  [3] AP Majtey, PW Lamberti, and DP Prato. Jensen-shannon divergence as a measure of distinguishability between mixed quantum states. *Physical Review A*, 72(5):052310, 2005.  [4] Peng Ding and Fan Li. Causal inference: A missing data perspective. *Statistical Science*, 33(2):214– 237, 2018.  [5] Jinsung Yoon, James Jordon, and Mihaela Schaar. Gain: Missing data imputation using generative adversarial nets. In *International Conference on Machine Learning*, pages 5689–5698. PMLR, 2018.  [6] Jinsung Yoon, James Jordon, and Mihaela van der Schaar. Ganite: Estimation of individualized treatment effects using generative adversarial nets. In *International Conference on Learning Representations*, 2018.  [7] Jinsung Yoon, Lydia N Drumright, and Mihaela Van Der Schaar. Anonymization through data synthesis using generative adversarial networks (ads-gan). *IEEE journal of biomedical and health informatics*, 24(8):2378–2388, 2020.  [8] Reza Shokri, Marco Stronati, Congzheng Song, and Vitaly Shmatikov. Membership inference attacks against machine learning models. In *2017 IEEE Symposium on Security and Privacy (SP)*, pages 3–18. IEEE, 2017.  [9] Cynthia Dwork, Aaron Roth, et al. The algorithmic foundations of differential privacy. *Found. Trends Theor. Comput. Sci.*, 9(3-4):211–407, 2014.  **Amendment 4 – 30.11.2022**  **Added University of Birmingham to the list of data processors.** |

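### Aim 3 revises its models when the propensity-score and instrumental-variable results differ, so agreement reached after that revision is not independent evidence against confounding

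*Protocol*

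**What the plan says.** The rule is in the protocol's Data/Statistical Analysis section under Aim 3, and Amendment 3 restates it, so it is in force. It has three parts.

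- **Diagnosis:** "If the results from the propensity score matching suffer from unmeasured confounding, they will differ from those of the instrumental analysis".
- **Action:** "If this is the case, these models will be refined with additional factors to achieve better adjustment and matching".
- **Reading of agreement:** "Where all approaches provide similar results, we can be more confident that the findings are accurate and reliable". The section on addressing confounding repeats this sentence.

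The Limitations section turns similarity into a decision rule for the assumption that all confounders are measured: "We will conclude the assumption has been met if high GP prescribers have a similar association with outcomes and the treatment itself". The same sentence adds two further conditions: treatment must be associated with the positive control and must not be associated with the negative control.

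Two other provisions bear on the point. The confounding section says: "Further steps will be taken to examine the validity of treatment effect estimates using positive and negative controls". Amendment 2 adds a multivariable Cox analysis, of which it says: "Estimates will be adjusted for pre-specified variables thought to confound the relationship between treatment and adverse events". That commitment to pre-specified variables is made for the multivariable analysis. The refinement rule for the PS analysis is left as it was.

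**The concern.** The plan uses one comparison for two purposes. The PS–IV difference decides whether the models are changed, and the PS–IV similarity then supports the conclusion that confounding is under control. A check that has already steered the model can no longer test it independently.

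The diagnosis is also too narrow. Two valid analyses can differ because the IV estimate is imprecise or because each method describes the effect in a different set of patients. They can also differ because the prescriber-preference instrument is invalid. In each case the plan as written would attribute the gap to confounding in the PS analysis and change the models.

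The remedy reaches only part of the problem it names. Further database factors can reduce confounding by something recorded but omitted, or by something with a recorded proxy. They cannot remove confounding by something the records do not hold.

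At stake is how Aim 3 is interpreted: whether a reported hazard ratio for a treatment harm may be described as confirmed by two approaches.

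**Working it through.** **1. The plan's own figure.** Sample size considerations gives 4,634 events for a 10% increase in event rate, 90% power and alpha 0.05. With 1:1 groups and a two-sided test, Freedman's formula is

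E = (1.960 + 1.2816)² × [(1.1 + 1)/(1.1 − 1)]² = 10.507 × 441 = 4,634.

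The figure reproduces exactly (Schoenfeld's formula gives 4,627). No stated number is in dispute; the fault is in the procedure.

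**2. The order of steps.**

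| Step | What the protocol does | What follows |
|---|---|---|
| a | Estimates the outcome effect by PS matching and by IV | Both treatment–outcome results are known |
| b | Takes a difference as PS confounding | Other causes of a difference are not considered |
| c | Adds factors to the models | The respecification was prompted by outcome results |
| d | Reads similarity as support for reliability and, with the controls, as meeting the assumption | The comparison that prompted step c is reused as evidence |

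The stated aim of step c is better adjustment and matching, but what sets it off is disagreement between outcome estimates, not covariate imbalance.

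**3. How often chance alone produces a gap.** This is an illustration on stated assumptions.

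Inputs from the protocol:
- 4,634 events (Sample size considerations).
- 1,200 intracranial haemorrhages and 216,000 falls (Feasibility counts).

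Assumptions, not in the protocol:
- Prescriber groups are of equal size.
- The proportion treated differs between high and low prescribers by d = 0.20 (range 0.30 to 0.10).
- Both methods are valid for the same effect, and the PS estimate is the efficient one.
- The yardstick is a 10% difference, ln(1.1) = 0.0953. It is borrowed from the power calculation; the plan states no threshold.

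Formulas:
- SE_PS = 2/√E
- SE_IV = SE_PS/d
- SD of the difference = √(SE_IV² − SE_PS²)
- P = 2 × [1 − Φ(0.0953/SD)]

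Worked case, E = 4,634 and d = 0.20:
- SE_PS = 2/√4,634 = 0.0294
- SE_IV = 0.0294/0.20 = 0.147
- SD = √(0.147² − 0.0294²) = 0.144
- 0.0953/0.144 = 0.66, so P = 51%

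| Events | SE_IV at d = 0.30 / 0.20 / 0.10 | P(gap > 10%) at d = 0.30 / 0.20 / 0.10 |
|---|---|---|
| 4,634 | 0.098 / 0.147 / 0.294 | 31% / 51% / 74% |
| 1,200 | 0.192 / 0.289 / 0.577 | 60% / 74% / 87% |
| 216,000 | 0.014 / 0.021 / 0.043 | <0.1% / <0.1% / 2.6% |

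The chance explanation is thus strong for the rarest primary outcome and weak for falls. The feasibility counts describe the whole expected population, so a 1:1 matched new-user analysis could have fewer events.

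**The case against.** The strongest reply is that PS–IV agreement does not stand alone. The Limitations section also requires the positive and negative controls to behave as expected, and Amendment 2 supplies a multivariable analysis with pre-specified variables. This stands: both are separate checks, and they limit how much weight the agreement carries. Neither prevents the PS models from being changed after outcome results are compared, and neither restores independence to that comparison.

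Second, a reader might infer that the hazard ratio will be pulled towards the IV result until the two match. The text does not say so. Its stated purpose is better adjustment and matching, no rule keeps a factor because of the direction in which it moves the estimate, and added confounders could move it either way. For the same reason no loss of confidence-interval coverage or type I error can be computed from the document; any such figure would need a selection rule that the plan does not contain.

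Third, a reader might say that the plan treats agreement as proof. Aim 3 claims only greater confidence. The Limitations wording is firmer, but it is conditional on the controls.

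Fourth, refinement is not futile. The records hold many further codes, and a recorded but omitted confounder can be adjusted for. This is correct, and it is why the point is limited to confounders with no record and no proxy.

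Fifth, the list of added factors, the size of difference that counts and the number of rounds may be in a statistical analysis plan that is not shown. That is accepted, and the point does not rest on their absence. It rests on the trigger and the reading of agreement, which the protocol itself states.

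**Conclusion.** The concern holds in a bounded form. As written, the protocol lets a comparison of outcome estimates prompt respecification and then uses the same comparison as support for validity. It also ascribes to confounding a difference that may come from imprecision, a different target population or an invalid instrument. Agreement reached after refinement is therefore not independent confirmation, though the control outcomes and the Amendment 2 multivariable model still give partial, separate evidence.

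The size depends on the outcome. Under the assumptions in the working, chance alone produces a gap above 10% in 51% (31–74%) of studies at 4,634 events and in 74% (60–87%) at 1,200 haemorrhages, but in under 3% at 216,000 falls. These percentages rest on an assumed instrument strength and a borrowed yardstick, and they measure how often a false signal could arise, not how far a hazard ratio would shift. The circularity itself, and the limit on what recorded factors can repair, do not shrink with sample size.

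**What to change.** In Aim 3, and in its restatement in Amendment 3:

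1. Delete the step that refines the models when the PS and IV results differ.
2. Settle the PS covariates before any treatment–outcome result is seen, and revise them only on covariate balance.
3. Report the unrefined PS and IV estimates and their difference with a 95% confidence interval.
4. If they differ beyond chance, state that unmeasured confounding, an invalid instrument or a different estimand cannot be excluded.
5. Label any later refit post hoc, and do not count it towards similarity of results in Aim 3, the confounding section or the Limitations decision rule.

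The cost is protocol wording only; no extra data are needed. The downside is that some outcomes will be reported as unresolved.
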